## Abstract

**Background:**

Population aging has sharply increased the prevalence of disability, imposing a substantial public health burden. Early identification of high-risk older adults and preventive interventions are crucial for promoting healthy ageing.

**Objective:**

This study aims to evaluate the effectiveness of a digital platform-based stratified intervention in delaying functional decline and reducing the incidence of disability among older adults in a real-world community setting.

**Methods:**

This multi-center, assessor-blind, randomized controlled trial will enroll 238 participants aged 65 years and older from eight healthcare community centers. Participants will be stratified by disability-risk level and randomized 1:1 to either a digital platform based, multi-domain intervention or usual care. The platform integrates evidence-based components, with intensity matched to low, moderate, or high risk of disability. Intervention lasts 6 months, with periodic reassessment of disability risk, with risk-dependent adjustment of the intervention plan. The primary outcome is the Short Physical Performance Battery (SPPB) score, while secondary outcomes include the incidence of disability, changes in disability risk scores, and adherence to the intervention.

**Conclusion:**

This study will evaluate the digital, risk-stratified, multidomain intervention designed to prevent disability in community-dwelling older adults. If effective, the findings will provide actionable evidence for integrating digital tools and personalized strategies into community-based geriatric care, advancing sustainable approaches to healthy aging and reducing the disability burden in rapidly aging societies.

**Study protocol registration:**

http://clinicaltrials.gov, Identifier NCT07508813.

## Introduction

1

Due to the acceleration of aging and changes in disease spectrum, disability has become an increasingly severe public health problem (1). Functional disability is generally defined as dependency in performing daily activities which are categorized into basic activities of daily living (BADL) and instrumental activities of daily living (IADL) due to physiological, psychological, or social factors (2, 3). A growing number of older adults, as their ages advance, most typically experience a decline in health or a gradual loss of the ability to perform basic yet essential daily activities, such as bathing or doing housework (4). The prevalence of disability among older adults in China was 26.4%, which is higher than in the US (15.6%) and the UK (18.3%) (5, 6). Disability among older adults is associated with a substantial decline in quality of life, increased healthcare expenditures, elevated mortality, and considerable caregiving and economic burdens for families and society (6–9).

Early identification of individuals at risk of disability could help guide targeted intervention strategies (10), and the implementation of preventive interventions is essential for promoting healthy ageing. Generally, disability risk refers to the predicted likelihood of future functional decline or development of BADL and/or IADL limitations among older adults who have not yet developed established disability. While various tests and prediction algorithms have been used to classify older adults into different categories of functional risk (10, 11), in this study, disability risk is operationally assessed using a self-developed and validated risk prediction model based on multidimensional risk factors.

Traditionally, multidomain interventions—including physical exercise (12, 13), nutritional guidance (14), and chronic disease management (15)—have been proven effective in delaying functional decline among high-risk older adults. However, traditional community-based programs often face significant challenges, such as high human resource costs, limited geographical accessibility, and difficulty in maintaining long-term adherence. In the era of global ageing, digital technology has emerged as an important and useful tool to overcome various challenges associated with aging, such as reduced physical and cognitive function (16, 17). For instance, technology-supported programs such as the LETHE trial combine smartphone applications, smartwatches, and digital coaching to deliver multimodal lifestyle interventions targeting dementia risk reduction (18). Similarly, the INSPIRE ICOPE-CARE program in France implemented a large-scale digital screening and monitoring system based on the WHO Integrated Care for Older People (ICOPE) framework (19). These findings highlight the potential of digital health interventions to overcome traditional barriers (20). Nevertheless, the implementation of digital interventions in geriatric populations requires careful consideration of technological literacy and accessibility (21, 22). Older adults with lower educational attainment, limited financial means, or reduced digital literacy may face barriers to using smartphones or internet-based services, potentially leading to their exclusion. To address this digital divide (23), digital platforms for older adults should be designed with simplified interfaces and integrated with human support from community staff or family caregivers.

Beyond the challenges of digital accessibility, important evidence gaps persist in current digital health research. Most available interventions have been developed around a single disease or clinical scenario, for example, post-hip fracture rehabilitation or dementia prevention. Others focus on only selected aspects of physical or cognitive function. These approaches may overlook the comprehensive functional health status of older adults living in the community. Moreover, risk-based intervention pathways have rarely been embedded into digital platforms, making it difficult to deliver tailored support according to different levels of disability risk. Another limitation is that many previous studies were not conducted as rigorous multicenter randomized controlled trials, which weakens the external validity of their findings. More evidence is also needed on whether such interventions can be implemented in real-world community settings, especially in rapidly aging low- and middle-income countries such as China.

In response to these limitations, this study will develop a digital platform-based stratified intervention program for preventing disability risk in community-dwelling older adults. To address potential barriers related to technological literacy and accessibility, the intervention is designed as a supported model, where community health staff and family caregivers can assist older adults in engaging with the digital platform. Through a multicenter randomized trial, we aim to evaluate a digital health platform that integrates repeated risk assessment, predictive modeling, and individualized intervention recommendations. The specific aims are as follows: (1) to develop a stratified disability risk intervention program; (2) to determine whether stratified digital intervention can delay functional decline and reduce new-onset disability; and (3) to assess participants’ adherence to the digital platform under real-world community conditions.

## Methods and analysis

2

### Study design and settings

2.1

#### Design

2.1.1

This study is designed as a randomized, assessor-blinded, parallel-group, multicenter trial. Eligible participants will be randomly allocated in a 1:1 ratio to either the intervention group or control group. The elderly in the intervention group will receive a digital platform-based stratified intervention, and the control group will receive usual care. To ensure a balanced distribution of baseline characteristics and minimize potential confounding effects, stratified randomization will be employed based on the level of disability risk. The study protocol is developed in accordance with the Standard Protocol Items: Recommendations for Interventional Trials (SPIRIT) guidelines (24) to ensure transparency, completeness, and rigor methodology. The study flowchart is depicted in Figure 1, and the trial schedule is outlined in Table 1. The trial has been registered at ClinicalTrials.gov (NCT07508813) on Sep 24, 2025.

**Figure 1 fig1:**
[figure not shown]
Study flowchart.

**Table 1 tab1:** Time schedule of the trial process.

	Study period			
	Enrolment	Allocation	Post-allocation	
Time points	-t_1_	t_0_	t_1_	t_2_
Enrollment				
Eligibility screening	P			
Informed consent	P			
Disability risk factors collection	P			
Disability risk calculation	P			
Randomization and allocation		P		
Intervention			0–6 months	
Outcome measurement				
Short Physical Performance Battery (SPPB)		P	P	P
Incidence of disability				P
Disability risk score	P		P	P
Intervention adherence			P	P

#### Settings

2.1.2

This trial will be implemented in eight community healthcare centers in Zhejiang Province, China. Of these, five are located in Hangzhou City, representing urban communities, and three are located in Changxing County, representing rural communities. The inclusion of both urban and rural sites is intended to improve the representativeness of the study population and strengthen the generalizability of the findings. All participating centers provide primary healthcare services and have established routine contact with older adults living in the community, which will support participant recruitment, delivery of the intervention, and follow-up assessments.

### Participants

2.2

#### Inclusion criteria

2.2.1

Participants meeting all the following criteria will be eligible for inclusion:

(1) Aged 65 years or older;(2) Community-dwelling permanent residents;(3) Able to use a smartphone independently or with assistance from a primary caregiver;(4) Cognitively able to understand study procedures and communicate effectively;(5) Willing to participate and able to provide written informed consent.

To ensure accurate enrollment, the study team will verify the eligibility criteria during the initial screening interview. Smartphone usage will be confirmed by asking the participant or their primary caregiver about smartphone ownership and their ability to perform basic application operations. Cognitive ability and communication skills will be assessed by trained researchers based on the participant’s ability to engage in the screening conversation and comprehend the study procedures during the informed consent process. Willingness to participate will be strictly documented through the signing of the written informed consent form.

#### Exclusion criteria

2.2.2

Participants will be excluded if they meet any of the following criteria:

(1) Inability to independently perform Basic Activities of Daily Living (BADL) or Instrumental Activities of Daily Living (IADL) (25, 26). Any difficulty in performing one or more of these activities is considered indicative of disability.(2) Significant cognitive impairment, defined as an MMSE score <10 (27) or a clinical diagnosis of dementia;(3) Severe speech, hearing, or visual impairments that would interfere with communication or participation in the intervention;(4) Severe or terminal illness limiting life expectancy.

A clinical diagnosis of dementia was verified through participant self-report, caregiver proxy report, or review of available medical history. Speech, hearing, or visual impairments that could interfere with communication or study participation were identified by study staff through observation and interaction during face-to-face screening. Severe or terminal illness was determined based on self-reported medical history or caregiver interview.

Although the enrolled participants are currently independent (free of BADL/IADL limitations), they remain at risk for future functional decline due to advanced age. By focusing on primary prevention, this study will utilize a validated prediction model to quantify the varying levels of underlying disability risk among this population.

#### Termination and suspension criteria

2.2.3

Participants may be withdrawn from the study under the following conditions:

(1) Withdrawal of consent or refusal to continue participation during the study period;(2) Loss to follow-up, defined as inability to contact the participant after three telephone attempts and failure to reach the participant through community healthcare workers;(3) Occurrence of serious adverse events that necessitate discontinuation of participation.

#### Recruitment strategy

2.2.4

To facilitate sufficient enrollment, the research team will recruit participants through multiple channels. Study information will be disseminated by displaying posters at community healthcare centers and activity centers. In addition, community health workers and family physicians will assist in identifying and contacting potentially eligible older adults. Health education activities will also be organized to introduce the study to the target population. Older adults who are willing to participate will subsequently be screened for eligibility by trained members of the research team. Written informed consent will be obtained from all participants prior to enrollment. Participants will be informed of the study objectives, procedures, potential risks, and their rights to withdraw at any time without penalty.

#### Sample size calculation

2.2.5

The sample size calculation was based on the expected difference in Short Physical Performance Battery (SPPB) scores between the intervention and control groups. In a published study of community-dwelling older adults in China, the average baseline SPPB score of 1,014 older adults was (8.92 ± 2.11) (28). For the expected between-group difference, a 1-point difference in SPPB was selected as the target clinically meaningful effect based on previous evidence that most estimates of substantial change for the SPPB ranged from 0.99 to 1.34 points (29). On this basis, the mean SPPB score was assumed to be 8.92 in the control group and 9.92 in the intervention group. Using PASS software, and assuming a two-sided *α* of 0.05 together with a power of 90%, the required number of participants was estimated to be 95 per group, corresponding to 190 participants in total. Considering a potential dropout rate of 20%, the sample size was adjusted to 238 participants.

Preliminary data further suggested that the proportions of older adults at high, moderate, and low risk of disability were approximately 1:5:4. Based on this distribution, the final sample is expected to comprise about 24 high-risk participants, 120 moderate-risk participants, and 94 low-risk participants.

### Randomization and blinding

2.3

#### Randomization sequence

2.3.1

Before randomization, eligible participants will undergo a baseline disability risk assessment using a disability risk prediction model that we previously developed and externally validated. The model produces a continuous predicted probability of disability for each participant. Two cut-off values were identified using the maximally selected rank statistics method and applied to classify participants into low-, moderate-, and high-risk groups. Within each stratum, participants will be allocated in a 1:1 ratio to either the intervention group or the control group.

The stratified randomization sequences will be generated using SPSS software by an independent researcher who will not participate in recruitment, intervention implementation, or outcome evaluation. A separate randomization list will be prepared for each disability risk stratum to maintain balance between the intervention and control groups across different risk levels.

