#### Allocation concealment

2.3.2

Allocation concealment will be maintained through a centralized randomization process. The randomization lists will be kept securely by the independent researcher who will have no role in participant recruitment, enrollment, intervention delivery, or outcome evaluation, or data analysis.

After completion of the baseline assessment and confirmation of the participant’s disability risk level, the enrolling investigator will contact the independent researcher and provide the relevant risk-stratification information. The independent researcher will then assign the participant to the intervention or control group based on the corresponding pre-generated randomization list for that risk stratum. Members of the research team responsible for recruitment, baseline assessment, intervention delivery, and outcome evaluation will not have access to the randomization sequences before group assignment. This procedure is intended to preserve allocation concealment and reduce the risk of selection bias.

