Analyses of secondary outcomes will be selected according to the type and distribution of each variable. Continuous outcomes will be analyzed using mixed-effects models or repeated-measures methods, as appropriate. For categorical outcomes, including the occurrence of disability, between-group comparisons will be conducted using chi-square tests, and logistic regression models may be used to estimate odds ratios with corresponding 95% confidence intervals. Potential confounders or clinically relevant baseline variables may be included in multivariable models when adjustment is warranted. Urban/rural residence will be considered in the adjusted analyses where appropriate. Subgroup or sensitivity analyses by urban/rural residence will be conducted, if sample size permits, to explore whether intervention effects differ between urban and rural participants.

Missing data will be handled using multiple imputation or likelihood-based methods under the missing-at-random assumption. All analyses will be conducted using R version 4.0.3 and SPSS version 29.0 (IBM Corp., Armonk, NY, USA). Statistical tests will be two-sided, with statistical significance defined as *p* < 0.05.

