The use of a digital platform is another important feature of this study, as it may improve the feasibility, scalability, and sustainability of the intervention. Digital health technologies are increasingly viewed as promising approaches to support healthy aging by improving access to care, enabling continuous monitoring, and facilitating self-management among older adults (34). Evidence from previous studies also suggests that digital interventions can improve chronic disease management, health-related knowledge, self-efficacy, and health behaviors (34–36). However, the use of digital health tools in older adults requires careful consideration of accessibility, equity, and the digital divide (22, 23). Therefore, researchers and policymakers should ensure that digital tools are equitable, unbiased, accessible, and responsive to the needs of older adults (21). In the present study, the digital platform enables real-time monitoring of adherence, automated feedback, and personalized recommendations, which may help improve participant engagement and intervention effectiveness. To minimize digital exclusion, several age-friendly design features were incorporated into the platform, including large-font interfaces, pictorial instructions, and simple instructional videos. In-person assistance was also provided by healthcare professionals at community health centers, and primary caregivers were allowed to help participants use smartphones when needed. In community settings where healthcare workforce capacity may be limited, this platform-based approach may also reduce dependence on face-to-face services and support the standardized delivery of multidomain interventions.

The primary outcome of this study is the Short Physical Performance Battery (SPPB) score. The SPPB is a well-established and validated tool for assessing lower-extremity physical performance in older adults and has been widely used to predict disability and other adverse health outcomes (37, 38). A 1-point increase in the SPPB score is generally considered clinically meaningful and has been associated with a lower risk of limitations in activities of daily living and future hospitalization (28, 29). Therefore, evaluating changes in SPPB scores before and after the intervention will allow this study to assess whether a digital, risk-stratified intervention can improve physical function and delay disability onset among older adults.

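### Allocation is stratified by disability risk only, so balance between urban and rural sites, which the protocol treats as relevant, is left to chance (minor)

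*Protocol article*

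**What the plan says.** All references are to the protocol article.

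- **Sites (2.1.2).** Eight centres take part. By area, "five are located in Hangzhou City, representing urban communities, and three are located in Changxing County, representing rural communities". The mix is deliberate, to make the sample more representative.
- **Stratification (2.1.1).** "stratified randomization will be employed based on the level of disability risk". The stated purpose is to balance baseline characteristics and limit confounding.
- **Lists (2.3.1).** "A separate randomization list will be prepared for each disability risk stratum to maintain balance between the intervention and control groups across different risk levels". That makes three lists, with 1:1 allocation within each.
- **Assignment (2.3.2).** "the enrolling investigator will contact the independent researcher and provide the relevant risk-stratification information". The assignment then comes from the list for that risk level. Centre and area are not part of the exchange.
- **Primary model (2.7).** The fixed effects are group, time point and their interaction, with a random effect for person. No area, centre or risk-stratum term is named.
- **Use of area in the analysis (2.7).** Residence is among the baseline characteristics to be compared. Adjustment for urban/rural residence is discretionary. "Subgroup or sensitivity analyses by urban/rural residence will be conducted, if sample size permits".

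**The concern.** The protocol stratifies in order to balance the arms, recruits two contrasting populations on purpose, and plans to look at results by area. Yet area plays no part in allocation, and its place in the analysis is left open.

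There are reasons why area could matter. Usual care is delivered by the local centres (2.4.2). Help with the platform is local too: "In-person assistance was also provided by healthcare professionals at community health centers" (Discussion). If rural and urban participants change differently over six months and the arms have different rural shares, part of that difference enters the treatment contrast. Whether to adjust would then be decided after the imbalance is visible, which invites dispute. At stake are some precision and the credibility of the comparison.

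**Working it through.** **1. The plan's own figure.** From 2.2.5: difference 1 point, SD 2.11, two-sided α 0.05, power 90%. The noncentral-t calculation gives power 0.898 at 94 per arm and 0.901 at 95, so 95 per arm and 190 in total. For 20% dropout, 190 / 0.8 = 237.5, rounded up to 238. The plan's figure reproduces, and nothing below changes it.

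**2. Inputs for the balance check.** From the document: N = 238, allocation 1:1, eight centres of which three are rural. Assumed, because the document does not give it: equal recruitment, so 238 / 8 = 29.75 per centre and 3 × 29.75 ≈ 89 rural participants (88 to 90 after rounding). Also assumed: 119 per arm.

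**3. Chance difference in rural share.** If X is the number of rural participants in the intervention arm, X is hypergeometric (119 drawn from 238, R of them rural).
- Difference in share = (2X − R) / 119.
- Var(X) = R(238 − R) / (4 × 237). For R = 89 this is 89 × 149 / 948 = 13.99, so SD(X) = 3.74.
- SD of the difference = 2 × 3.74 / 119 = 0.063, about 6 percentage points.
- A difference of 10 points needs |2X − R| ≥ 11.9. The result depends slightly on whether R is odd or even:

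| Rural participants | Smallest count difference that qualifies | Probability |
|---|---|---|
| 88 | 12 | 0.139 |
| 89 | 13 | 0.108 |
| 90 | 12 | 0.141 |

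A simulation of the three risk lists (24, 120 and 94, exact 1:1 in each, centre ignored) gives about 12%. With an assumed uneven recruitment in which 80% of participants are urban, it gives about 6%.

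**4. What an imbalance does to the estimate.** The planned contrast is on change in SPPB, so a constant urban-rural difference in level largely cancels. What remains is the share difference times the urban-rural difference in change. With 10 points of imbalance, 0.10 × 1 = 0.1 SPPB point for each full point by which the areas differ in change. The area difference in change would have to equal the whole 1-point target effect to move the estimate by a tenth of that target.

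**5. What adjustment costs.** With 10 points of imbalance and a rural proportion of 89 / 238 = 0.374, the squared correlation between arm and area is 0.10² × 0.25 / (0.374 × 0.626) = 0.0107. The variance inflation is 1 / (1 − 0.0107) = 1.011, about 1%.

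**6. What is gained in power.** As a rough guide for a comparison of SPPB level at 95 per arm, with assumed centre intraclass correlations of 0.01, 0.05 and 0.10: power is 90.5%, 90.6% and 90.8% if centre is ignored, and 90.7%, 91.8% and 93.1% if it is balanced or adjusted for. The chance contribution of centre to the estimate has an SD of about 0.03, 0.06 and 0.09 points.

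**7. What six lists achieve.** With permuted blocks of 4 (assumed), the arms differ by at most 2 per list, hence by at most 3 × 2 = 6 within an area, or 6 / 119 ≈ 5 points of rural share. With blocks of up to 6, the limits are 3 × 3 = 9 and 9 / 119 ≈ 7.6 points. Either way a 10-point difference is ruled out.

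**The case against.** Stratifying by risk level alone is a defensible choice. Risk level drives the intensity of the intervention and the reassessment schedule, and with about 24 high-risk participants each added factor makes small cells. Usual care follows common national and provincial standards, data collection is meant to be uniform across sites, and nothing in the document says that care or assessment differs by centre. The imbalance is random, the test remains valid, and section 2.7 already mentions adjustment for residence. The analysis plan, which is not shown, may make that adjustment firm. All of this stands, and it is why the point is minor. It does not remove the mismatch between the stated purpose of stratification and a factor that the protocol singles out but leaves open at both allocation and analysis.

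A reader might infer more, and the documents do not support it:

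- **That the comparison is biased.** Chance imbalance under concealed randomisation is not bias.
- **That later adjustment repairs the loss only in part.** Step 5 shows that it recovers nearly all of it, at about 1% in variance.
- **That the urban/rural subgroup analysis is materially weakened.** A 38:50 split of 88 rural participants keeps 4 × 38 × 50 / 88² = 98% of the information of an even split. The limit is the number of rural participants, which stratification does not change.
- **That imbalance within single centres argues for area lists.** Under equal recruitment, some centre splits 2:1 or worse in about 42% of trials, but six area-by-risk lists lower that only to about 32%. It is no support for this remedy.

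**Conclusion.** The point holds as a minor design weakness. Allocation ignores area, and the described primary model contains neither area nor centre, so urban/rural balance is a matter of chance. Under equal recruitment, a rural-share difference of 10 points or more has a probability of about 11 to 14%. It is lower (about 6%) if 80% of participants are urban. Recruitment per centre, block size and centre correlation are not in the document, so these figures rest on the assumptions stated.

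The consequence is small: a modest loss of precision, and an avoidable argument over whether to adjust. The validity of the trial and its sample size of 238 are not in question.

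**What to change.** - **Section 2.3.1 (with 2.1.1 and 2.3.2 to match).** Have the independent researcher prepare six lists, three risk levels by urban/rural area, in permuted blocks of varying size not disclosed to the sites. The enrolling investigator then reports area together with risk level.
- **Section 2.7.** Replace the discretionary wording by prespecifying risk stratum and urban/rural area (or centre) in the primary mixed model. Because the contrast is on change, let these terms also interact with time point; a main effect alone adjusts level.
- **If recruitment is under way,** use the six lists for the remaining allocations. **If allocation is complete,** the model terms alone suffice.

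The cost is three more lists, one more item in a call that is made anyway, and one amended sentence. The strata become somewhat smaller: with equal recruitment, the high-risk level would have about 24 × 3/8 = 9 rural and 15 urban participants. Stratifying by all eight centres is not advised, since it would need 8 × 3 = 24 lists with about 24 / 8 = 3 high-risk participants per centre.
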